## Abstract

**Background:**

With an ageing population, older persons become a larger part of the hospital population. The incidence of delirium is high in this group, and experiencing delirium has major short- and long-term sequelae, which makes prevention crucial. During delirium, a disruption of the sleep-wake cycle is frequently observed. Melatonin plays an important role in the regulation of the sleep-wake cycle, so this raised the hypothesis that alterations in the metabolism of melatonin might play an important role in the development of delirium. The aim of this article is to describe the design of a randomised, placebo controlled double-blind trial that is currently in progress and that investigates the effects of melatonin versus placebo on delirium in older, postoperative hip fracture patients.

**Methods/Design:**

Acutely hospitalised patients aged 65 years or older admitted for surgical repair of hip fracture are randomised (n = 452) into a treatment or placebo group. Prophylactic treatment consists of orally administered melatonin (3 mg) at 21:00 h on five consecutive days. The primary outcome is the occurrence of delirium, to be diagnosed according to the Confusion Assessment Method, within eight days after start of the study medication. Secondary outcomes are delirium severity, measured by the Delirium Rating Scale; duration of delirium; differences in subtypes of delirium; differences in total length of hospital stay; total dose of antipsychotics and/or benzodiazepine use during delirium; and in-hospital complications. In the twelve-month follow up visit, cognitive function is measured by a Mini-Mental state examination and the Informant Questionnaire on Cognitive Decline in the Elderly. Functional status is assessed with the Katz ADL index score (patient and family version) and grip strength measurement. The outcomes of these assessments are compared to the outcomes that were obtained during admission.

**Discussion:**

The proposed study will contribute to our knowledge because studies on the prophylactic treatment of delirium with long term follow up remain scarce. The results may lead to a prophylactic treatment for frail older persons at high risk for delirium that is safe, effective, and easily implementable in daily practice.

**Trial registration:**

Dutch Clinical Trial Registry: NTR1576

## Background

Delirium is the most frequent neuropsychiatric syndrome observed in acutely admitted elderly patients in hospitals and is associated with an increased risk of dementia, mortality, and institutionalisation [1]. The incidence of delirium varies depending on the methods employed and the population studied but were shown to be 53% in a former cohort of hip fracture patients studied by our group [2]. Most clinical patients with delirium suffer from pre-existing cognitive impairment based upon neurodegenerative brain lesions. The prophylactic treatment or early treatment of delirium may prevent these patients from experiencing accelerated cognitive decline [3]. Thus, prevention is crucial.

The current prophylactic treatment of delirium consists of both pharmacological treatment with antipsychotics and non-pharmacological interventions, of which the latter seems the most effective [4]. Pharmacological treatment with antipsychotics often leads to serious side effects such as drowsiness and concomitant falls. In addition, up to a ten-fold increase in risk of cerebrovascular accidents in the first week of treatment was found and a higher frequency of prolonged QT-interval or extra pyramidal symptoms have been reported [5,6]. Given these serious side effects, safer treatment options are warranted. Recently, melatonin has been hypothesised to play a part in delirium, both as a biomarker and as a safe treatment option [7].

Melatonin, a hormone secreted by the pineal gland, plays an important role in the regulation of the sleep-wake cycle [8]. During delirium, disruption of the sleep-wake cycle, such as fragmented sleep during the night and sleepiness during the day, is frequently observed [9]. This trend raises the hypothesis that alterations in the metabolism of melatonin may play an important role in the development of delirium [10]. Elderly persons have decreased peaks of nocturnal melatonin concentrations [11]. Serum melatonin concentrations were also found to be lower with later nocturnal peak concentrations in elderly persons with insomnia as compared to age-matched controls without insomnia [12]. Additionally, a disturbed circadian pattern of melatonin secretion has been found in post-operative patients with delirium [13]. In another study among medical patients, differences in urinary melatonin metabolite concentrations were found during delirium and after recovery from delirium [14]. These results may suggest an association between delirium and a disturbed melatonin secretion pattern.

Investigations into the relationship between melatonin therapy and delirium have also been undertaken. One case report showed that exogenous administration of melatonin prevented the occurrence of delirium [15]. There are indications that melatonin is effective in the treatment of sleep-wake cycle disturbances in ICU patients and in patients with dementia [16,17]. Moreover, it has been demonstrated that treatment with melatonin increases total sleeping time and reduced sleep latency in elderly patients [18], and it enhances sleep time and night activity in patients with Alzheimer's dementia [19]. Recently, two randomised clinical trials on prophylactic treatment with melatonin have been performed. Both studies showed a reduction in the occurrence of delirium in medical and elective surgical patients [20,21]. However, no follow up data were available, and the potential of melatonin to prevent long term adverse events like dementia still remains unclear.

This paper describes the design of the study; "The effects of melatonin versus placebo on delirium in hip fracture patients", a trial currently in progress. The aims of the study are to investigate whether prophylactic treatment with melatonin will lead to a reduction in the occurrence of delirium in hip fracture patients and to study whether melatonin prevents long-term adverse outcomes.

## Methods and design

### Research questions

#### Primary research question

1] Is there a difference in the occurrence of delirium within eight days of hospital admission between hip fracture patients treated with melatonin or placebo?

#### Secondary outcome measures

2] Severity and duration of delirium.

3] Subtypes of delirium.

4] Length of hospital stay.

5] Additional use of benzodiazepines during delirium.

6] Total dose of haloperidol for the treatment of delirium.

7] In-hospital complications.

8] Cognitive and functional decline twelve months after hospital admission.

9] Mortality during hospital stay and twelve months after hospital admission.

### Study design

This study is a randomised, placebo-controlled, double blind, national, multicentre study with a one-year prospective follow-up. Figure 1 shows the design of the study. Informed consent is obtained from all patients or a legal representative in the case of cognitive impairment. Over five evenings, the patients receive the study medication consisting of a tablet containing either a placebo or 3 mg melatonin. Subsequently, daily assessment for the presence of delirium is performed, and the patients are followed for another three days. In total, each patient is observed for a minimum of eight days. For patients who are not delirious on day eight, daily assessments are stopped. For patients who are delirious by day eight, to evaluate duration of delirium, daily clinical assessments are continued until the symptoms of delirium are resolved or until the patient is discharged. Possible confounding factors including demography, fracture characteristics, type of anaesthesia, type of surgery and peri- and postoperative complications are registered for all patients. This study is carried out in compliance with the Helsinki Declaration. The Medical Ethics Committee (METC) of the Academic Medical Centre (AMC) has approved the study design, protocol and informed consent procedures. The executive board of Tergooihospitals has provided local feasibility approval.

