### Study population and recruitment

The study population consists of patients of 65 years and older who are admitted for the surgical treatment of hip fractures. Hip fractures are defined as fractures of the femoral neck, the trochanteric region or the proximal femur. Further inclusion criteria are enrolment within 24 hours of admission and the patient must be willing and medically able to receive the study medication according to the protocol for the duration of the study. Exclusion criteria are the inability to speak or understand Dutch, the concomitant use of melatonin and prior participation in this study.

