### Data collection

Demographic data, medical history and medication use are recorded. Once included in the study, patients are visited daily (and once during the weekend) for efficacy and safety evaluations by an experienced team of geriatric nurses and geriatricians. For the diagnosis of delirium, the Cognitive Assessment Method (CAM) is used [22,23]. The CAM was developed in 1990 and is a validated and widely used screening tool for the presence of delirium. When patients are delirious, the severity of delirium is examined using the Delirium Rating Scale-Revised-1998 (DRS-R-98). The severity of delirium is expressed as the maximum DRS-R-98 score during the delirium period. Subtyping is examined using the Delirium Symptom Interview [24] and the Delirium Motoric Checklist [25]. Cognitive and functional status and the presence of impairment prior to admission are assessed. Each patient and their primary caregiver are asked to complete questionnaires to assess the patient's pre-existent functional and cognitive state two weeks prior to hospital admission. Functional status is assessed using the 15-item Katz Activities of Daily Living (ADL) index score, based on the situation two weeks prior to admission, to be completed by the patient or their closest relative in cases of cognitive impairment. Impairment is calculated using the number of impaired ADLs [26].

Primary caregivers are asked to complete the Informant Questionnaire on Cognitive Decline short form (IQCODE-sf) [27] by recalling the situation two weeks prior to the hip fracture and comparing this with the situation ten years earlier. Patients with a mean score of 3.9 or higher are considered to have global cognitive impairment [28]. Grip strength of the dominant hand, as an objective measurement of functional status [29], is measured using hand-held dynamometry. The severity and number of comorbidities is scored using the Charlson comorbidity index [30]. At the time of discharge from the hospital the total amount of haloperidol and other antipsychotics used during hospital admission is recorded, also the length of stay and in-hospital complications are collected.

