### Statistics

Data will be primarily analysed according to the intention-to-treat principle and secondarily compared by per protocol analysis. To study the effectiveness of the melatonin treatment, the difference in the occurrence of delirium between patients treated with or without melatonin will be tested with Chi-square statistics. Continuous secondary outcome measures, if normally distributed, will be tested using a Students' t-test, otherwise Mann-Whitney tests will be employed. The duration of delirium will be tested using a log-rank test. Categorical outcome variables will be tested with a Chi-square test. Outcomes for patients who had delirium at day one of the study will be calculated separately. Subsequently, multivariable logistic regression will be used to compare differences between melatonin and placebo groups in the primary and in the secondary outcome measures.

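### Peri- and postoperative complications are labelled possible confounders although they can follow randomisation and in-hospital complications are a secondary outcome; if they enter the planned regression, the adjusted melatonin effect can be biased

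*Protocol article*

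**What the plan says.** Four places in the protocol article bear on this.

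- **Study design** lists what is recorded as potentially confounding: "Possible confounding factors including demography, fracture characteristics, type of anaesthesia, type of surgery and peri- and postoperative complications are registered for all patients". No other list in the article is called confounding.
- **Secondary outcome measures**, item 7, reads "In-hospital complications". Under Data collection these are gathered at discharge: "also the length of stay and in-hospital complications are collected".
- **Statistics** tests the primary outcome without adjustment: "the difference in the occurrence of delirium between patients treated with or without melatonin will be tested with Chi-square statistics". The intention-to-treat analysis comes first: "Data will be primarily analysed according to the intention-to-treat principle and secondarily compared by per protocol analysis". A further step follows: "Subsequently, multivariable logistic regression will be used to compare differences between melatonin and placebo groups in the primary and in the secondary outcome measures". No covariates are named.
- **Study population and recruitment** requires "enrolment within 24 hours of admission" in patients admitted for surgical treatment. The article does not say when surgery falls relative to randomisation or the first dose.

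**The concern.** One class of variable has two incompatible roles: something to control for, and something treatment may change and on which the arms will be compared. A baseline variable can be imbalanced by chance, and adjusting for it is harmless and often useful. A variable that treatment may alter is different, because holding it constant no longer estimates the full effect of assignment to melatonin.

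Three problems follow if complications become covariates.

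1. If melatonin reduces complications and complications provoke delirium, adjustment removes that part of the benefit.
2. Complications may result from delirium. For later outcomes such as mortality, they then lie on the path from treatment through delirium to the outcome. For delirium itself, the model would condition on a consequence of the outcome.
3. For secondary outcome 7, complications would stand on both sides of the model.

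At stake are the adjusted estimates for the primary and secondary outcomes, not the main test.

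**Working it through.** **Step 1. The plan's own figure.** Inputs from Power analysis: 50% versus 37%, two-sided alpha 0.05, power 80%, 226 per group.

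- Unpooled variance: n = (1.960 + 0.842)² × (0.50×0.50 + 0.37×0.63) / 0.13² = 224.4, so 225 per group.
- Pooled variance, with mean risk 0.435: n = [1.960×√(2×0.435×0.565) + 0.842×√(0.25 + 0.2331)]² / 0.13² = 227.1, so 228 per group.
- Power at 226 per group is 79.8%.

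The stated 226 is reproduced and is not contested. It belongs to the unadjusted comparison, whose odds ratio is (0.37/0.63)/(0.50/0.50) = 0.587.

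**Step 2. What adjustment would do.** The article gives neither complication rates nor the strength of their link to delirium, so both are assumed and varied. The model is logit P(delirium) = a + t×melatonin + b×complication, with b = ln(complication odds ratio). For each scenario, a and t are chosen so that the total effect stays at 50% versus 37%. The adjusted odds ratio is exp(t). The adjusted risk difference is standardised to the average complication rate of the two arms.

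*Worked case: complications 30% versus 20%, complication odds ratio 3.* Solving gives a = −0.320 and t = −0.447. Delirium risks without and with a complication are:

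- placebo: 0.421 and 0.685; check 0.7×0.421 + 0.3×0.685 = 0.50
- melatonin: 0.317 and 0.582; check 0.8×0.317 + 0.2×0.582 = 0.37

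Standardised to a 25% complication rate:

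- placebo: 0.75×0.421 + 0.25×0.685 = 0.487
- melatonin: 0.75×0.317 + 0.25×0.582 = 0.383
- difference: 10.4 points instead of 13.0

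The adjusted odds ratio is exp(−0.447) = 0.64. With 226 per group the standard error of t is 0.197, so Wald power is Φ(0.447/0.197 − 1.96) = 62%.

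**Step 3. The range.** Complication odds ratios run from 2 to 5.

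| Complications, placebo vs melatonin | Adjusted difference (points) | Adjusted odds ratio | Power of adjusted test |
|---|---|---|---|
| 30% vs 30% | 13.0 | 0.58 to 0.55 | 80 to 84% |
| 30% vs 25% | 12.2 to 11.1 | about 0.60 | 75 to 71% |
| 30% vs 20% | 11.3 to 9.2 | 0.62 to 0.66 | 68 to 55% |
| 40% vs 25% | 10.5 to 7.3 | 0.65 to 0.71 | 61 to 38% |

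In the first row melatonin does not act on complications and nothing is lost. The odds ratio there differs from 0.587 only because conditional and marginal odds ratios differ. The other rows lose part of a true effect. This calculation covers only the path from treatment through complications to delirium. Complications that result from delirium are not quantified.

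**The case against.** The strongest objection is that the article never says complications will be covariates. Study design says only that the listed factors are registered, and calls them possible confounders. Statistics names no covariates and does not refer back to that list. An unnamed covariate set in a condensed article may properly be left to the full protocol or the SAP. This stands: a reader might infer that the plan commits to complication-adjusted models, and the text does not support that. What remains is the label itself. It is a stated classification, not an omission, and it heads the only list on which a later covariate choice could draw.

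Other objections stand in part.

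- **Main analysis.** The intention-to-treat chi-square test and its sample size are untouched. A reader should not infer that the primary conclusion is at risk.
- **Timing.** A reader might infer that every listed complication follows randomisation, or that tablets begin on the evening of enrolment. The article supports neither. The Abstract speaks of postoperative patients, and some perioperative events could precede the first dose. However, postoperative complications collected up to discharge are not separated from earlier events, so the label still covers events that treatment could change.
- **Per-protocol analysis.** Randomisation does not fully protect this comparison, and recording clinical events may be useful there. That supports collecting complications, not treating them as confounders of the randomised comparison.
- **Magnitude.** The losses come from assumed effects of melatonin on complications. With a modest effect (30% to 25%) the loss is about 1 to 2 points, and with none there is none in this model.

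**Conclusion.** The point holds as a misclassification with a conditional consequence. The article names peri- and postoperative complications as possible confounders while counting in-hospital complications as an outcome, and it plans regression for all outcomes with the covariates left open. If complications enter those models, the adjusted melatonin effect can be biased, and the model for secondary outcome 7 is circular.

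The size cannot be derived from the article. It depends on the complication rates, on whether melatonin changes them, and on their link to delirium, all of which are assumed in the table above. The problem is confined to the regression that follows the main test. It should be corrected, but it does not threaten the design, the sample size or the primary test.

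**What to change.** 1. In Study design, take peri- and postoperative complications out of the confounding factors. Continue to collect them and keep them as secondary outcome 7.
2. In Statistics, state that treatment-effect models adjust only for study centre (the stratification factor) and variables fixed before randomisation. Suitable ones already collected include age, IQCODE-sf, Katz ADL, Charlson index and fracture type.
3. Type of anaesthesia and type of surgery are in the same list and may also be settled after randomisation. Use them as covariates only if they are fixed beforehand.
4. Label any complication-adjusted model as exploratory, and fit none where complications are the outcome.

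The cost is wording only. No new data are needed, and the sample size and primary test stay as they are.

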**Figure 1 F1:**
[figure not shown]
**Design of the RCT; inclusion of patients with hip fracture, 65 years and older**.

### Location and setting

The primary trial location is the surgical, orthopaedic or trauma surgery ward of the AMC in Amsterdam, The Netherlands. This is a major teaching hospital, containing 1002 beds. The secondary location is Tergooihospitals, a teaching hospital consisting of 630 beds at two locations, in Hilversum and Blaricum, The Netherlands.

### Study population and recruitment

The study population consists of patients of 65 years and older who are admitted for the surgical treatment of hip fractures. Hip fractures are defined as fractures of the femoral neck, the trochanteric region or the proximal femur. Further inclusion criteria are enrolment within 24 hours of admission and the patient must be willing and medically able to receive the study medication according to the protocol for the duration of the study. Exclusion criteria are the inability to speak or understand Dutch, the concomitant use of melatonin and prior participation in this study.

### Randomisation

A randomisation schedule, made by an independent statistician, is employed that is stratified by study centre and uses block randomisation of ten participants per block. The trial-pharmacist is the only one in possession of the randomisation list.

### Study medication

Study medication tablets all look the same and are packaged in small pots labelled according to Good Manufacturing Procedure (GMP) guidelines. The concentration is a fixed concentration as both placebo and melatonin are manufactured by and obtained from the same pharmaceutical company. On prescription by [name], [name] or [name], a pot can be collected at the pharmacy when a patient is included.

### Data collection

Demographic data, medical history and medication use are recorded. Once included in the study, patients are visited daily (and once during the weekend) for efficacy and safety evaluations by an experienced team of geriatric nurses and geriatricians. For the diagnosis of delirium, the Cognitive Assessment Method (CAM) is used [22,23]. The CAM was developed in 1990 and is a validated and widely used screening tool for the presence of delirium. When patients are delirious, the severity of delirium is examined using the Delirium Rating Scale-Revised-1998 (DRS-R-98). The severity of delirium is expressed as the maximum DRS-R-98 score during the delirium period. Subtyping is examined using the Delirium Symptom Interview [24] and the Delirium Motoric Checklist [25]. Cognitive and functional status and the presence of impairment prior to admission are assessed. Each patient and their primary caregiver are asked to complete questionnaires to assess the patient's pre-existent functional and cognitive state two weeks prior to hospital admission. Functional status is assessed using the 15-item Katz Activities of Daily Living (ADL) index score, based on the situation two weeks prior to admission, to be completed by the patient or their closest relative in cases of cognitive impairment. Impairment is calculated using the number of impaired ADLs [26].

Primary caregivers are asked to complete the Informant Questionnaire on Cognitive Decline short form (IQCODE-sf) [27] by recalling the situation two weeks prior to the hip fracture and comparing this with the situation ten years earlier. Patients with a mean score of 3.9 or higher are considered to have global cognitive impairment [28]. Grip strength of the dominant hand, as an objective measurement of functional status [29], is measured using hand-held dynamometry. The severity and number of comorbidities is scored using the Charlson comorbidity index [30]. At the time of discharge from the hospital the total amount of haloperidol and other antipsychotics used during hospital admission is recorded, also the length of stay and in-hospital complications are collected.

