### Follow-up assessments

Three months after admission, a home visit is made by a trained nurse, to perform a Mini-Mental State Examination (MMSE) [31] and to measure the grip-strength of the dominant hand. The MMSE is a validated 30-point questionnaire-based test that is used to screen for cognitive impairment. Twelve months after the hospital admission, the patient is visited again at home by a trained nurse to perform a MMSE test and a Katz ADL index score and to assess grip-strength. Additionally, the patient's primary caregiver is asked to complete the caregiver's version of the Katz ADL index score and the IQCODE-sf by telephone.

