### Power analysis

The primary endpoint is the occurrence of delirium during the first eight days after the start of study medication. In the AMC, the incidence of delirium in patients after surgical repair of hip fracture is now over 50% [2]. The prevention of delirium has been previously assessed in several studies. At the time this study began, other studies using medication prophylaxis had not shown any significant reduction in the incidence of delirium. Assuming an absolute reduction of 13%, with a 50% incidence of delirium in the control group and an incidence of 37% in the intervention group, we require 226 patients per group (452 patients in total) to detect differences with a power of 80% and a two-sided alpha of 0.05.

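### The admission IQCODE-sf is itself a ten-year change rating, so comparing the twelve-month score with it as before and after does not in general give cognitive decline since the fracture

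*Protocol article*

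**What the plan says.** All references are to the protocol article.

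- **Data collection, admission form.** The caregiver completes the IQCODE-sf "by recalling the situation two weeks prior to the hip fracture and comparing this with the situation ten years earlier". The score is used to classify pre-existing impairment: "Patients with a mean score of 3.9 or higher are considered to have global cognitive impairment".
- **Follow-up assessments, twelve months.** "the patient's primary caregiver is asked to complete the caregiver's version of the Katz ADL index score and the IQCODE-sf by telephone". The article gives no reference time for this second form.
- **Abstract, Methods/Design.** At twelve months "cognitive function is measured by a Mini-Mental state examination and the Informant Questionnaire on Cognitive Decline in the Elderly". After the functional measures are listed, the text continues: "The outcomes of these assessments are compared to the outcomes that were obtained during admission".
- **Secondary outcome measures, item 8.** The outcome is "Cognitive and functional decline twelve months after hospital admission".
- **Statistics.** Continuous secondary outcomes are compared between arms with a t-test or a Mann-Whitney test, and multivariable logistic regression follows. No formula for change from admission is given.

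**The concern.** A before-and-after comparison makes sense for an instrument that records a state. The Katz index, as described under Data collection, is one: it counts impaired activities at a point in time. The IQCODE-sf at admission is different, because each score already describes a change over an interval. The abstract applies the same comparison with admission to both kinds of instrument.

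The distance between two change ratings is the decline since the fracture only if the two intervals start at the same moment. Otherwise it contains decline from some other period. A patient who worsened during the year could then show no difference, or an apparent improvement. This bears on the cognitive part of item 8 and so on the article's second aim, the prevention of long-term adverse outcomes.

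**Working it through.** **The plan's own figure.** The article gives no figure for the IQCODE-sf outcome. Its only calculation is for delirium, "with a 50% incidence of delirium in the control group and an incidence of 37% in the intervention group", which leads to 226 per group. With unpooled variance, n = (1.960 + 0.842)² × (0.50 × 0.50 + 0.37 × 0.63) / 0.13² = 225 per group. The pooled form gives 228, and the power at 226 per group is 0.798. The stated size reproduces within rounding and variance convention. Nothing below touches it.

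**Inputs for the check.** The admission window comes from Data collection. The yearly declines are assumptions in arbitrary score units, and a score is taken to be linear in the decline over its window. The two weeks between the rated state and the fracture are ignored.

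- e = decline in the oldest year, from ten to nine years before the fracture
- M = decline in the following nine years, up to the fracture
- p = decline in the year after the fracture, the quantity item 8 asks for

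Admission score = e + M.

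**Twelve-month score minus admission score, for each possible reference time:**

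1. Ten years before the twelve-month call (same form reused): (M + p) − (e + M) = p − e.
2. Fixed at ten years before the fracture: (e + M + p) − (e + M) = p.
3. The pre-fracture state: p − (e + M).

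**Numbers, with M = 9 × 0.1 = 0.9:**

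| e | p | 1: form reused | 2: fixed anchor | 3: since fracture |
|---|---|---|---|---|
| 0 | 0.3 | 0.30 | 0.30 | −0.60 |
| 0.05 | 0.3 | 0.25 | 0.30 | −0.65 |
| 0.1 | 0.3 | 0.20 | 0.30 | −0.70 |
| 0.1 | 0.1 | 0.00 | 0.10 | −0.90 |

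Only the second reference time returns p in every row. The first returns p when e = 0 and falls short by e otherwise. The third gives a negative number, which reads as improvement, although every patient in the table worsened.

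**Between arms.** Take the same pre-fracture history in both arms (e = 0.1, M = 0.9), with p = 0.2 on melatonin and 0.3 on placebo.

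- Reference time 1: (0.2 − 0.1) − (0.3 − 0.1) = −0.1
- Reference time 2: 0.2 − 0.3 = −0.1
- Reference time 3: (0.2 − 1.0) − (0.3 − 1.0) = −0.1

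The pre-fracture terms cancel, so the expected arm contrast is the same under all three.

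**Precision.** Let r be the correlation between the two scores, and assume equal standard deviations. Relative to the variance of the twelve-month score alone (set to 1), the difference has variance 2(1 − r), and the twelve-month score adjusted for the admission score has 1 − r².

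| r | Difference | Twelve-month alone | Adjusted |
|---|---|---|---|
| 0 | 2.00 | 1 | 1.00 |
| 0.3 | 1.40 | 1 | 0.91 |
| 0.5 | 1.00 | 1 | 0.75 |
| 0.8 | 0.40 | 1 | 0.36 |

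The ratio of adjusted to difference is (1 − r²) / [2(1 − r)] = (1 + r)/2, which never exceeds 1. Subtraction is worse than ignoring the admission score whenever r is below 0.5. The documents give no value for r.

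**The case against.** The case on the other side is substantial, and it limits the point in five ways.

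- **A reader might infer that the comparison fails whichever reference time is used.** It does not. An anchor fixed ten years before the fracture gives exactly the post-fracture decline. With the form reused, the shortfall is only e, which may be small; nothing in the article supports a constant pace of decline over the decade.
- **A reader might infer that the treatment comparison is biased.** The documents do not support this. Tests are between arms, allocation is randomised, and pre-fracture history balances in expectation. On a linear scale the contrast is unchanged.
- **A reader might infer that the article commits to subtracting the scores.** It says only that outcomes are compared. Subtraction is the natural reading of a comparison with admission meant to show decline, but it is an inference.
- **A reader might infer that the IQCODE-sf is the only cognitive measure with an admission counterpart.** Data collection lists no admission MMSE. Yet the abstract's sentence on comparison with admission follows a list that includes the MMSE, so one may exist. The MMSE is in any case measured at three and twelve months.
- **The missing reference time for the telephone form is no error in itself.** A condensed article can leave such an instruction to the full protocol.

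All five stand as limits. They do not remove the core: the article defines the admission score as a change rating and states a comparison with it as the route to decline. Its wording most naturally makes the ten years relative to the moment being rated, so reusing the form leads to p − e. Randomisation does not rescue the within-patient meaning or the precision lost when r is low.

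**Conclusion.** The point holds in limited form. The comparison with admission, as stated, does not in general isolate cognitive decline after the fracture. With the ten-year form reused it is off by the decline in the oldest year: 0 to 0.1 against a true 0.3 in the first three rows, and the whole effect when the two years are equal. With a since-fracture form the difference has no useful meaning for a patient. With a fixed anchor it is correct, but the article does not describe one.

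The damage is to how decline is read within patients and to precision: subtraction doubles the variance at r = 0 and breaks even with the unadjusted score at r = 0.5. These sizes rest on a linear scale, assumed yearly declines and equal standard deviations; the cancellation between arms also rests on linearity. The matter concerns one instrument of one secondary outcome.

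**What to change.** State in the analysis that the within-patient difference between the two IQCODE-sf scores will be neither tested nor interpreted as decline. Compare the twelve-month score between arms in a linear model with the admission IQCODE-sf as baseline covariate. Name that model explicitly, since the only multivariable model in the Statistics section is logistic. Keep one stated reference time for the twelve-month form in all patients. The cost is a sentence or two in the analysis: the admission score is already collected, no visit is added, and in the linear model the adjusted comparison is never less precise than the difference.

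Re-anchoring the twelve-month form to the pre-fracture state is optional and is a trade-off in a running trial. It would make the score a direct rating of decline since the fracture. However, the 3.9 cut-off, which the article applies to the ten-year form, should then not be used on it, and patients already followed on the old wording would need separate analysis.
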